| This is a prospective pilot randomised trial to study the effectiveness of prednisolone versus methotrexate in achieving clinical or radiological complete response for women with IGM. The study will be conducted in NUH. This study evaluates the effectiveness of each drug in terms of clinical and/or radiological response, time to resolution as well as total number of flares over a period of one year follow-up. This study can potentially identify a more effective treatment with fewer side effects for women with IGM as well as personalize drug choices for patients who are at risk of frequent flares. |  |
| **HYPOTHESIS AND OBJECTIVES** |  |
| Hypothesis |  |
| The hypothesis is that methotrexate has a higher 6-month clinical or radiologically complete response with lesser side effects than prednisolone. The time to clinical or radiological response is shorter in the methotrexate arm compared to prednisolone arm. Relapse and time to first relapse is lower and longer in the methotrexate arm compared to prednisolone arm. |  |
| Primary Objectives |  |
| The primary objective is to evaluate the 1) Proportion of patients who achieved clinical or radiological complete response at 6 months 2) Time to clinical response and time to radiological response, and 3) Proportion of patients with relapse in one year within affected breast between each arm. |  |
| Secondary Objectives |  |
| The secondary objectives include evaluation of:   1. Side effects 2. Frequency of percutaneous or surgical intervention required 3. Potential biomarkers that may predict response to treatment: eg IL-6, CRP and neutrophil to lymphocyte ratio (NLR) 4. Patient reported outcome measures 5. Validate survey instrument for IGM patients |  |
| Potential Risks and benefits |  |
| End Points – Efficacy |  |
| Benefits expected for the patient are the total remission of IGM or reduced relapsed/flare of IGM. |  |
| End Points – Safety |  |

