| *Screening*  After patient is consented to the study, a baseline blood test (32mls, including pregnancy test, Hepatitis B test, Hepatitis C test, full blood count, liver function test and renal function test) and chest X-Ray will be conducted during the baseline visit to assess for eligibility prior to enrolment to the treatment phase. Additional research blood (14.5mls, 1 tablespoons) will be collected at this baseline visit for research purposes. Patient may be exempted from chest X-Ray and/or blood test if patient has done the same test within 30 days.  Baseline demographics and relevant clinical variables of patients will be collected. The following demographic and clinical variables will be collected: age of presentation, pre-menopausal or post-menopausal status, parity / breastfeeding status, concomitant rheumatic conditions, personal or family history of tuberculosis, smoking or alcohol intake, presenting complaint, unilateral or bilateral involvement, affected quadrant of the breast, duration of symptoms and previous antibiotics prescription for treatment of IGM.  Information on comorbidities will be evaluated to ensure suitability for both treatment arms prior to recruitment. Examples include drug allergies, plans for pregnancy, ongoing infection, previous history of cancer, previous tuberculosis, epilepsy, diabetes, hypertension, kidney, liver, cardiac problems, osteoporosis, glaucoma, peptic ulcers, previous side effects to either prednisolone or methotrexate.  If patient fulfilled all the eligibility criteria after screening assessment, she will be randomised to either of the treatment arm.  If patient did not meet the full eligibility criteria (eg. Pregnant, hepatitis carrier or abnormalities in renal or liver panels), she will not proceed to the treatment phase. The data collected and additional blood samples will be kept for analysis.  *Treatment Phase*  Patient will be scheduled to attend a clinical visit (T_0_) to either breast or rheumatology clinic if she meets all eligibility criteria for the initiation of treatment dose. There will be a window period of ± 7 days for this clinical visit. Patient is required to complete a pre-treatment quality of life online survey (approximately 10-15 minutes).  Patient will be scheduled for blood test (8mls, 0.5 tablespoons) and clinical visits to either breast or rheumatology clinic at the 1^st^ (T_1_), 2^nd^ (T_2_), 3^rd^ (T_3_) and 6^th^ (T_4_) month to assess their signs and symptoms, and drug compliance. There will be a window period of ± 14 days for each of these clinical visits. Additional research blood (14.5mls, 1 tablespoons) will be collected on the 1^st^ (T_1_) and 6^th^ (T_4_) months.  Patients are required to undergo a breast ultrasound to assess for their radiological response during the 3^rd^ (T_3_) clinical visit. A window period of ± 14 days will be applicable. The initial measurement of the breast lesion or mass will be recorded in three dimensions – i.e. anteroposterior, superior-inferior, mediolateral measurements. If complete clinical and radiological complete response has been achieved on the 3^rd^ (T_3_) visit, the doctor will discontinue the drug in a safe manner and no further breast ultrasounds will be required. If the patient’s symptoms or signs have not resolved by the 3^rd^ (T_3_) clinical visit, patient’s drug dosage will be assessed by the rheumatologist and treatment may be continued up to the 6^th^ (T_4_) month period and a repeat breast ultrasound will be required at the 6^th^ (T_4_) month. If symptoms have not resolved by the 6^th^ (T_4_) month of clinical visit, the patient’s drug dosage may be up-titrated or will be given an addition of a second therapy, i.e. combination therapy of steroid and methotrexate may be used. For clinical visits mention above, it will coincides with standard care visit.  During the clinical visits, Tingting Hu et al’s “M- score” will be adopted to grade the severity of the disease. M score is being calculated during clinical visits for IGM patients regardless of trial status for objective follow up. This is a common practice. For this study, the score will be administered by their attending healthcare professional (not limited to breast surgeons, investigators, or breast care nurses).  The M-score will be the sum of the following:  1) Mass score  2) Erythema score  3) Fistula score  4) Pain score  5) Quality-of-life (QoL) score  The scoring criteria were defined as follows:  1) Mass score: 0 for the absence of mass by palpation; 1 for mass ≤3 cm by palpation; 2 for mass >3 cm by palpation.  2) Erythema score: 0 and 2 for the absence and presence of erythema, respectively  3) Fistula: 0 and 2 for the absence and presence of fistula, respectively  4) Pain Score: 0 for Visual Analogue Score (VAS) 0-2; 1 for VAS 3-5; 2 for VAS 6-10  5) QoL score: 0 for absence of effects on QoL; 1 for mild effects on QoL, where the patient does not require medical assistant; 2 for serious effects on QoL, where the patient requires medical assistant  The total M-score ranges between 0 and 10 and serves as a quantitative and objective measurement of the severity of the symptoms.  The primary endpoint will be the clinical complete response (cCR) rate, which is defined as the proportion of patients who have an M-score of ≤ 1 at ≤1 years after treatment.  The secondary endpoints will be as follows:   - - The time to cCR, defined as the median time to cCR post randomisation.   - The treatment failure (TF) rate, defined as the proportion of patients with TF at 1 year post randomisation. The TF status will be defined as follows:     - If the patient has an M-score ≥6 before randomisation, TF is defined as the M-score remaining at ≥6 at 1 month post randomisation.     - If the patient has an M-score between 4 and 5 before randomisation, TF is defined as the M-score remaining at ≥4 and never being lower than 4.     - If the patient has an M-score <4 at baseline but never reaches cCR after randomisation, TF is defined as the M-score being >5 at the follow-up and remaining above 5 for one month. - Relapse rate, which is defined as the proportion of patients who have M-score >4 among the patients who achieved CR.   Throughout the course of the study, there are possible flares and relapse of the disease. Flares will be defined as any increase in M-score or lesion size on ultrasound whilst on therapy. While relapse will be defined as recurrence of symptoms or signs of IGM in the breast after previously experiencing complete resolution following therapy. If relapse occurs, patient will restart the same treatment arm for 6 months.  In the event of flares, blood test (8mls, 0.5 tablespoons) and additional research blood (14.5mls, 1 tablespoons) will be collected and the allocated treatment for the patient will be up-titrated by the doctor. In event of relapse, treatment for the patient will be reinitiated as per the allocated arm.  Additional research blood samples collected during the trial will be used for gene expressing profiling to identify unique patterns of gene expression that can be used to diagnose IGM and predict its treatment response.  Regardless of treatment arm, patient will be monitored by either breast surgeon or rheumatologist. Surgeons will assess for eligibility into trial, clinical reviews, and ultrasound breasts interpretation. Rheumatologists will be monitoring for drug side effects and titration if required. In event of failure of medical therapy, surgeons will have to intervene accordingly for aspiration or surgical drainage. In the event where patients require aspiration or surgical drainage during the study, methotrexate or prednisolone should be continued unless there is evidence of sepsis. The frequency of aspiration or surgical intervention will be recorded as events during the study.  Whenever the disease has been resolved during the study period, the balance medication and/or packaging will be retrieved to do medication accounting and checking for adherence to assigned treatment arm.  If side effects were to develop, doctors will evaluate the severity of the side effects and withdraw the patients from the trial if needed. |  |

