| De-identified blood samples will be analysed and stored in NUH Tissue Repository. Recruitment and follow-up survey data will be collected electronically via NUHS REDCap. Only study team members with delegated rights will be able to access the data under the supervision of PI and Site-PI. All survey data will be collected electronically via FormSG. A copy of de-identified data will be stored in a secured server at NUH. |  |
|  |  |
| **SAMPLE SIZE AND STATISTICAL METHODS** |  |
| Determination of Sample Size |  |
| The prevalence rate of IGM in NUH is currently at 10 to 15 patients per year. Based on a stepped rule of thumb, a minimum sample size of 30 will provide at least 80% power to detect a medium standardised effect size of between 0.3 to 0.7 based on a randomised two-group comparison (Machin et al, 2021). Assuming a 20% attrition rate, the sample size required for this study is 36 patients. This will be rounded up to a sample size of 40 patients over a period of 36 months. |  |
| Statistical and Analytical Plans The primary outcome of 6-month clinical or radiological complete response will be compared between arms using Chi-square test. The effect estimate will be quantified in terms of difference in proportion as well as relative risk (RR) and their associated 95% confidence interval (CI). The secondary outcomes of time-to clinical or radiological response and time-to-relapse will be evaluated via the Kaplan-Meier method. The differences in survival curves will be compared using log rank test, with the effect estimate quantified in terms of hazard ratio and its 95% CI. The primary analysis of this trial will be based on Intention-to- Treat (ITT). A Per Protocol (PP) analysis will be performed on all patients who have completed 6 months of treatment regimen as a sensitivity analysis.  Chi square test will be used to evaluate the proportion of side effects and requirement for percutaneous or surgical intervention during treatment between arms. Modified Poisson regression will be used to identify clinical or biomarkers that are associated with treatment response and quantify the effect in terms of RR.  Patient reported outcomes will be reported via a survey on FormSG, conducted online. The questions will be adapted from SF36 V1 Singapore version and EORTC-BR23. Below are the domains to be compared:   - - General Health   - Physical Health   - Mental Health   - Body Image   - Sexual Image   - Breast Health |  |
| **ETHICAL CONSIDERATIONS** |  |

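### The protocol names conflicting primary endpoints: complete response at 6 months in Section 11.2, M-score response by 1 year in Section 6.3, and three primary objectives in Section 2.2

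*Protocol*

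**What the plan says.** Three sections of the protocol say what is primary.

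- Section 2.2 (Primary Objectives) lists three items. The first is "Proportion of patients who achieved clinical or radiological complete response at 6 months", the second is "Time to clinical response and time to radiological response", and the third is the share of patients who relapse in the affected breast within a year.
- Section 6.3 (Study Visits and Procedures, Treatment Phase) names the clinical complete response (cCR) rate as the primary endpoint, defined as "the proportion of patients who have an M-score of ≤ 1 at ≤1 years after treatment". It has no radiological component. Time to cCR, treatment failure and relapse rate follow as secondary endpoints.
- Section 11.2 (Statistical and Analytical Plans) states: "The primary outcome of 6-month clinical or radiological complete response will be compared between arms using Chi-square test". It then states: "The secondary outcomes of time-to clinical or radiological response and time-to-relapse will be evaluated via the Kaplan-Meier method".

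Section 6.3 also provides that, if symptoms persist at the 6-month visit (T4), the dose may be raised or a second therapy added, and that "combination therapy of steroid and methotrexate may be used".

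**The concern.** A confirmatory comparison needs one primary endpoint, fixed before the data are seen. Here two sections each name a different single primary, and a third names three. The versions differ in component (clinical only, or clinical or radiological), in time (6 months, or up to 1 year) and in number.

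Section 8.5 makes the trial open label, and the M-score is given by the attending healthcare professional. If the versions disagree, someone who already knows the results by arm could report whichever is more favourable and cite a section of the protocol in support. The 1-year version also answers a different question, because it can count responses that came after treatment was intensified or the other arm's drug was added.

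**Working it through.** **Step 1. The statements side by side.**

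| Place in the protocol | Component | Time | Time to response | Relapse |
|---|---|---|---|---|
| 2.1 Hypothesis | clinical or radiological | 6 months | in the hypothesis | in the hypothesis |
| 2.2 Primary Objectives | clinical or radiological | 6 months | primary | primary (proportion in one year) |
| 6.3 Treatment Phase | clinical only, M-score ≤1 | up to 1 year | secondary (time to cCR) | secondary (relapse rate) |
| 11.2 Statistical and Analytical Plans | clinical or radiological | 6 months | secondary | secondary (time to relapse) |

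The rationale for the study design (Section 1.2) and the design summary (Section 5.1) give the same two components as 11.2 but no time point. No section ranks the versions or says which prevails. The sample size paragraph (Section 11.1) names no endpoint and no response rates, so it does not show which one the trial was sized for.

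**Step 2. Can the difference change a patient's status?**

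| Patient | 6.3 | 11.2 |
|---|---|---|
| First M-score ≤1 between months 6 and 12, not radiologically clear at 6 months | responder | non-responder |
| Radiologically clear at 6 months, M-score never ≤1 within the year | non-responder | responder |
| M-score ≤1 at 6 months | responder | responder |

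The table uses M-score ≤1 as the clinical component throughout, since 6.3 gives the only definition of it. The first two rows are classified in opposite ways. A first-row patient may have responded after up-titration or combination therapy.

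**Step 3. Size.** Section 5.1 plans 20 patients per arm, and the primary analysis is by intention to treat. One reclassified patient moves the arm's rate by 1/20 = 5 percentage points, two by 2/20 = 10 and three by 3/20 = 15. The difference between arms moves by 5 points times the net imbalance in reclassified patients. If equal numbers change in both arms, it does not move. The documents do not allow the number of such patients to be estimated.

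**Step 4. Which version do the planned assessments support?** T4 is a compulsory clinical visit in Figure 1, and the M-score is taken at clinical visits. After T4 the only scheduled visit is month 12. That visit may be a teleconsultation (Follow up Phase), while the mass item of the M-score requires palpation. For the radiological component, Figure 1 leaves the T4 ultrasound to the doctor's discretion, and 6.3 requires it only if symptoms or signs have not resolved by month 3. The 6-month version therefore needs no new visit, but it does need a rule for patients without a T4 ultrasound.

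**The case against.** The strongest reply is that the protocol does have a primary endpoint. Section 11.2 ties one outcome to one test, the hypothesis and first objective match it, and 6.3 is the outlier. That stands. A reader might infer that the trial has no primary endpoint at all, and the text does not support this. The reply does not remove the contradiction, because 6.3 calls a different measure the primary endpoint in plain terms and 2.2 lists two further items as primary. A later analysis plan could choose between them, but the protocol would still contradict itself.

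The wording in 6.3 is also loose. Reading it as a response at any time up to a year is natural, though it could mean status at one year. The conflict survives either reading, because neither is 6 months and neither has a radiological component. Nor is every late response a combination response, since up-titration alone is also allowed.

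Three stronger inferences are tempting and are not supported:

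- **Inflated error from three primary tests.** This would need each objective in 2.2 to be tested as a co-primary. Section 11.2 plans one primary test.
- **A calculated dilution of the effect at one year.** The 80.7% and 94% in the dose rationale describe patients who responded well or improved. They are not 6-month complete-response rates, so they cannot show how much the 1-year version would shrink the difference.
- **Patients who already meet cCR at entry.** No minimum M-score is required, and 6.3 foresees the case "If the patient has an M-score <4 at baseline but never reaches cCR after randomisation". But scores below 4 include 2 and 3, and the document gives no share for patients entering at 1 or less.

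**Conclusion.** The protocol contradicts itself on its primary endpoint and should be corrected before any outcome data are examined. Section 6.3 conflicts with 11.2, the hypothesis and the first objective on both component and time. Section 2.2 conflicts with 6.3 and 11.2 on the status of time to response and relapse. Each patient whose status depends on the version is worth 5 points in an arm of 20. How many there will be, and in which arm, is unknown, so no direction or total size of bias can be claimed. The conclusion rests on the text alone and on no assumed response rate.

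**What to change.** State one primary endpoint identically in Sections 2.2, 6.3 and 11.2. The smallest change is to bring 6.3 and 2.2 into line with 11.2: complete response, clinical or radiological, at the 6-month visit (T4), in all randomised patients, with M-score ≤1 as the clinical component. List cCR by 1 year, time to response, treatment failure and relapse as secondary. Because the T4 ultrasound is not planned for everyone, add a sentence on how the radiological component counts for patients who have none at that visit.

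A switch to clinical response alone at T4 would be a fourth definition and would leave the hypothesis, design rationale and Section 5.1 in conflict with it. A minimum M-score at entry is a separate eligibility decision and is not needed here. It would also have a price: Section 11.1 expects 10 to 15 patients a year, or 30 to 45 over 36 months, against a target of 40.

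The cost is a wording amendment, submitted to the review board as Section 12.2 requires. No visit is added, since T4 is already compulsory.

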| This research study is to determine the effectiveness of prednisolone and methotrexate for IGM patients over a period of one year, in terms of clinical and radiological response. Recruitment will be conducted in National University Hospital (NUH) for patients diagnosed with IGM.   1. **Prednisolone**   Prednisolone is a member of the corticosteroid drug class. The hormones known as corticosteroids are produced naturally by the body and support overall health. Prednisolone can help lessen swelling, redness, and itching as well as signs of inflammation. Additionally, prednisolone can be used to treat ailments like, asthma, allergies, eczema, psoriasis, lupus and rheumatoid arthritis. (<https://www.healthhub.sg/a-z/medications/482/prednisolone>) As IGM is an inflammatory breast disease, prednisolone is often used as a first-choice therapy. However, it is associated with multiple side-effects, frequent recurrences after discontinuation of therapy and may be associated with impaired quality of life.   1. **Methotrexate**   Methotrexate is a medication that lowers immune system hyperactivity. It is used to treat several autoimmune illnesses, including inflammatory myositis, juvenile idiopathic arthritis, rheumatoid arthritis, systemic lupus erythematosus (SLE), psoriasis, and psoriatic arthritis. Methotrexate functions as a disease-modifying anti-rheumatic medication (DMARD) in the treatment of arthritis, assisting in the reduction of pain, swelling, and long-term joint damage.  (<https://www.healthhub.sg/a-z/medications/178/methotrexate>)  Presently, methotrexate is considered second-line therapy and appears to have fewer side-effects. To date, there are a few reports describing the use of methotrexate at different stages in the disease. For example, switching of steroid therapy to methotrexate after a lack of response to corticosteroid treatment or adverse reactions, or following a relapse of disease on steroid therapy or used as combination with steroids during the initial treatment. However, methotrexate monotherapy or in combination with low doses of corticosteroids were rarely reported. Nonetheless, methotrexate use was found to be associated with a high complete response rate of up to 75% and relapse rates are significantly lower than prednisolone and surgeries. |  |
| Rationale and Justification for the Study |  |
| Rationale for Doses Selected |  |

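### Relapse has two incompatible definitions and two ranks, and its rate is taken among responders only, a comparison that randomisation does not protect

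*Protocol*

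**What the plan says.** Section 6.3 (Treatment Phase) lists among the secondary endpoints: "Relapse rate, which is defined as the proportion of patients who have M-score >4 among the patients who achieved CR". It does not say whether CR here is clinical, radiological or both. The same section defines the clinical complete response rate (cCR) as "the proportion of patients who have an M-score of ≤ 1 at ≤1 years after treatment".

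The paragraph after that list gives a second rule: "relapse will be defined as recurrence of symptoms or signs of IGM in the breast after previously experiencing complete resolution following therapy". This rule has no M-score threshold. The sentence that follows it restarts the allocated treatment for 6 months when relapse occurs.

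The rank also varies. Section 2.2 gives as the third part of the primary objective: "Proportion of patients with relapse in one year within affected breast between each arm", with no restriction to responders. Section 11.2 says: "The secondary outcomes of time-to clinical or radiological response and time-to-relapse will be evaluated via the Kaplan-Meier method".

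Section 2.1 expects the arms to differ on both response and relapse: "methotrexate has a higher 6-month clinical or radiologically complete response with lesser side effects than prednisolone", and "Relapse and time to first relapse is lower and longer in the methotrexate arm compared to prednisolone arm".

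**The concern.** Anyone counting relapses has two rules in the same section and gets different counts from the same patients. The text that starts re-treatment stands beside the rule without a threshold, so the clinical action can change whether a patient ever meets the other rule. For an outcome that appears in the primary objective and in the hypothesis, the definition has to be fixed before data are seen.

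The second issue is the denominator of the 6.3 rate. Achieving CR happens after randomisation, and the protocol hypothesises that it differs by arm. The two responder groups need not be alike. If one drug brings more hard-to-treat patients into response, and such patients also relapse more, that arm can show the higher relapse rate even when the drugs do not differ in their effect on relapse.

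**Working it through.** The protocol states no relapse rate, effect size or power for relapse, so there is no planned figure to reproduce.

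**Step 1. Do the two definitions agree?** The M-score components in section 6.3 are mass 0/1/2, erythema 0/2, fistula 0/2, pain 0/1/2 and quality of life 0/1/2. That gives 3 × 2 × 2 × 3 × 3 = 108 combinations: 4 score ≤1, 40 score 2-4 and 64 score >4. These are counts of possible states, not of expected patients.

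| Course | M-score >4 after CR | Any recurrence after complete resolution |
|---|---|---|
| Resolved, then erythema alone (2) | no | yes |
| Resolved, then fistula (2) + mass >3 cm (2) = 4 | no | yes |
| cCR with residual mass ≤3 cm (1), then ≥5 | yes, if CR means cCR | no, never completely resolved |

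The rules differ in threshold and in starting state, so neither is contained in the other.

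**Step 2. Does the re-treatment text matter?** If recurrence at 2-4 counts as relapse for management, treatment restarts at that point. Such a patient may then never exceed 4. The >4 count therefore partly reflects re-treatment.

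**Step 3. Rank.** Section 2.2: primary. Section 6.3: relapse rate secondary. Section 11.2: time to relapse secondary.

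**Step 4. Responder-only denominator.** From the protocol: 20 patients per arm (section 5.1), and 75% as the upper figure for complete response on methotrexate (section 1.1: "high complete response rate of up to 75% and relapse rates are significantly lower than prednisolone and surgeries").

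Assumptions, not in the documents:
- CR in the other arm is 50% or 60%.
- Half the patients in each arm (10) are easy to treat and half (10) are hard to treat.
- CR is 90% in easy patients in every arm. In hard patients it is 60%, 10% or 30%, giving overall CR of (90+60)/2 = 75%, (90+10)/2 = 50% or (90+30)/2 = 60%.
- Relapse risk after CR depends only on patient type, so there is no drug effect on relapse.

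Responders, easy + hard, are 9 + 6 = 15, 9 + 1 = 10 or 9 + 3 = 12.

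Rate among responders = (easy responders × easy risk + hard responders × hard risk) / responders.

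For risks of 10% (easy) and 40% (hard):
- CR 75%: (9 × 0.10 + 6 × 0.40)/15 = 3.3/15 = 22%
- CR 50%: (9 × 0.10 + 1 × 0.40)/10 = 1.3/10 = 13%
- CR 60%: (9 × 0.10 + 3 × 0.40)/12 = 2.1/12 = 17.5%

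| Risk easy/hard | CR 75% | CR 60% | CR 50% |
|---|---|---|---|
| 10%/40% | 22% | 17.5% | 13% |
| 20%/40% | 28% | 25% | 22% |
| 20%/60% | 36% | 30% | 24% |
| 20%/20% | 20% | 20% | 20% |

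With unequal risks the arm with fewer responders looks better each time. With equal risks the difference vanishes.

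**Step 5. Which measure repairs this?** Take CR 75% versus 50%.
- Relapses over all randomised, 10%/40%: 3.3/20 = 16.5% vs 1.3/20 = 6.5%. For 20%/60%: 5.4/20 = 27% vs 2.4/20 = 12%. Changing only the denominator still favours the arm with fewer responders, because a patient who never responds cannot relapse.
- Sustained response over all randomised, 10%/40%: (15 − 3.3)/20 = 58.5% vs (10 − 1.3)/20 = 43.5%. For 20%/60%: (15 − 5.4)/20 = 48% vs (10 − 2.4)/20 = 38%. This favours the arm that is better by construction.

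**The case against.** A reader might infer that the protocol breaks its own intention-to-treat rule. The text does not show that. Section 11.2 applies intention-to-treat to the primary analysis, the only primary outcome it names is 6-month response, and both 6.3 and 11.2 list relapse outcomes as secondary. What stands is the conflict of rank with section 2.2.

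A reader might also infer that relapse is counted only among responders throughout, or that the comparison is known to be biased. The responder denominator is literal only in the 6.3 rate; section 2.2 states none. The bias needs response and relapse to share prognostic factors, which the documents do not quantify, and it is zero when relapse risk is the same in all patients. If methotrexate has more responders, as hypothesised, any such distortion would work against methotrexate.

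It is fair to add that relapse presupposes earlier response under either rule, so a rate among responders is a recognised descriptive measure. Details such as the at-risk set for the Kaplan-Meier curves may properly sit in an analysis plan that is not shown, and this is a 40-patient pilot. These arguments limit the denominator point. They do not touch the definitions: an analysis plan could choose one for counting, but it could not align the protocol's re-treatment text with it.

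**Conclusion.** The conflict of definitions is certain from the text and makes the relapse outcome wrong as written. Two rules in one section classify the same patient differently, in both directions, and CR is not tied to a clinical or radiological criterion. (The second direction, a rise from M-score 1 to 5 or more, reads CR as cCR.) The conflict of rank between 2.2 and 6.3/11.2 is equally plain.

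The denominator point is conditional. The 6.3 rate compares post-randomisation subsets that the protocol expects to differ, so randomisation does not protect it. It can favour the arm with fewer responders, by 6 to 12 percentage points in the assumed 75% versus 50% scenarios (28% vs 22% up to 36% vs 24%) and by 3 to 6 points for 75% versus 60% (28% vs 25% up to 36% vs 30%). It gives no difference under equal relapse risk. These figures illustrate a mechanism and do not predict this trial's result.

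**What to change.** - State one relapse definition for the analysis, say which CR (clinical, radiological or both) opens the at-risk period, and report the other definition as a sensitivity analysis.
- Give relapse one rank across sections 2.2, 6.3 and 11.2.
- For the between-arm comparison, add sustained response in all randomised patients: CR within the protocol's stated response window, no relapse through T5, and never reaching CR counted as failure. Name the window, because 6.3 allows up to 1 year while 2.2 and 11.2 use 6 months.
- Keep the responder-only rate as descriptive.
- The investigators must reconcile the re-treatment text with the analysis definition. No trigger is proposed here.

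The cost is amendment wording and one derived variable. There are limits. The composite mixes response with relapse. It includes the effect of any up-titration or combination therapy after month 6, which 6.3 permits. The T5 visit may be a teleconsultation while mass is scored by palpation, so some T5 M-scores may be incomplete.
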